### Implementation phase

Guided by the Theoretical Domains Framework (TDF) [38], the implementation phase participants will be asked to complete an online survey using REDCap to identify facilitators and barriers to the introduction of HRV-F into standard practice. Survey responses will be used to establish how best to translate the HRV-F intervention into healthcare practice for adults with SCI. Survey participation will be voluntary and anonymous. Semi-structured interviews will be conducted via telephone with health professionals who have delivered the HRV-F intervention, or who would deliver the HRV-F, if it was introduced into standard practice. This will include professionals such as psychologists, physiotherapists, nurses, rehabilitation physicians, social workers and occupational therapists. The semi-structured interviews will be used to reflect on the facilitators and barriers identified during the survey and to review the practicality and acceptability of potential solutions to identified barriers. The participants who completed the HRV-F will also be asked two open-ended questions after they complete HRV-F:

“What have been the main challenges for you with learning and doing your therapy?” and “If there was one or two things that could be done differently to improve your therapy, what would they be?” The implementation at scale model to support systems-level diffusion (see Fig. 3), will also inform this work [39]. Articulating a robust implementation strategy addressing challenges faced by health professionals and stakeholders will streamline future translation, preventing costly trial and error attempts in implementing HRV-F into practice.

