### Procedure

The RCT will involve the 120 adults being randomly allocated to either a HRV-F group or a no-treatment control group. Both groups will be similarly assessed over a period of 12-months, that is, at baseline, 10 weeks post-baseline (immediately after the HRV-F treatment for the intervention group), and at 6 and 12-month post-baseline. To test the feasibility of the RCT, the first 10 RCT participants with SCI who meet inclusion and exclusion criteria (5 in the HRV-F and 5 in the control arm) will be monitored for adherence to the HRV-F therapy and assessment, and for any barriers to the intervention and control group membership. The implementation study will involve conducting a mixed methods approach (qualitative and quantitative) to establish how best to translate HRV-F interventions into the community.

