### Setting

Participants living in the community will be recruited from outpatient clinics of the two participating sites, that is, Royal North Shore Hospital (RNSH) and Royal Rehab, NSW, or they will approach the research team after viewing study advertisements posted at targeted social and commercial media outlets. Assessment and the HRV-F intervention will only be conducted at the RNSH campus in which the testing laboratory, a dedicated air-conditioned laboratory, is situated. Participants in the HRV-F group will also complete some treatment components in their home setting. The implementation phase participants from the SSCIS Network will be asked to complete an online survey. The SSCIS Network members include clinicians, consumers, government policymakers and representatives from non-government organisations. Ten semi-structured interviews will be conducted via telephone with health professionals who have delivered the HRV-F intervention, or who would deliver the HRV-F if it was introduced into standard practice.

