### Power analyses

For the primary outcome measures, assuming an α = 0.05, a small to moderate effect size of 0.3 (based on results from studies in other conditions), with 2 groups (HRV-F and control) of 50 in each group and four assessment periods, estimated statistical power is 0.99 [67]. To allow for reduced participant numbers due to loss to follow-up, sickness, death, or unwillingness to continue, we will recruit up to 120 participants.

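### The two open questions on therapy challenges go only to participants who completed HRV-F, so the participant feedback is selected towards completers

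*Protocol article*

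**What the plan says.** Under Implementation phase, the protocol article adds a participant element to the implementation study: "The participants who completed the HRV-F will also be asked two open-ended questions after they complete HRV-F". The first question is "What have been the main challenges for you with learning and doing your therapy"; the second asks what might be done differently to improve the therapy.

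The rest of the implementation study draws on other people. For the survey, "the implementation phase participants will be asked to complete an online survey using REDCap to identify facilitators and barriers". Under Setting, these respondents come from a state network: "The SSCIS Network members include clinicians, consumers, government policymakers and representatives from non-government organisations". The same section says "Ten semi-structured interviews will be conducted via telephone with health professionals who have delivered the HRV-F intervention", or who would deliver it if it entered standard practice.

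Under Procedure, the first 10 trial participants, 5 of them on HRV-F, "will be monitored for adherence to the HRV-F therapy and assessment, and for any barriers to the intervention and control group membership". Under Power analyses, the recruitment target allows for reduced numbers "due to loss to follow-up, sickness, death, or unwillingness to continue".

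**The concern.** The article does not merely leave open who is asked. It fixes the respondents and makes completion the condition. People who give up a therapy because of travel, illness or time burden are well placed to describe those obstacles, and under this rule they are not asked.

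The programme is demanding enough for this to matter. HRV-F training describes six two-hour face-to-face sessions and four remote ones, and notes the risk of sickness in this population. Setting places the face-to-face work at one campus. Home practice asks for about 20 minutes of breathing exercises twice a day.

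What is at stake is the usefulness of the participant feedback for planning community translation. If it comes only from people who finished, it may say little about why others did not.

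**Working it through.** No figure in the plan bears on this point, so there is nothing to reproduce. The check sets the sections side by side and then asks whether a size can be derived.

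**1. Does any other source put an equivalent question to HRV-F participants who stop?**

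- *Procedure:* barriers are monitored in the first 10 participants, whether or not they complete. On the HRV-F side that is 5 of 60 = 8.3%. The other 55 are not covered.
- *Home practice:* weekly telephone support, a homework log and app-based adherence apply to the whole HRV-F group. They can show that someone stopped. No question on the reason is described.
- *Table 1 and the self-reported satisfaction section:* the 10-week items are not limited to completers, but they are two Likert scales on health services received and change in health, not on obstacles to the therapy.
- *Diaries:* these cover costs, adverse events and symptom ratings.
- *Survey:* network members include consumers, but nothing says they received HRV-F. The survey is anonymous, so it could not identify people who stopped.
- *Interviews:* some interviewees delivered HRV-F and may have seen why people struggled. That is second-hand evidence.

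None of these puts the two questions to a participant who stops.

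**2. Could those participants be reached?** Control of bias keeps every randomised participant in the analysis regardless of treatment received. Someone who stops therapy but remains in the study is still due for the 10-week assessment, and Data management gives each participant a personal REDCap link. The contact routes exist.

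**3. Can the size be calculated?** Let *s* be the share of the HRV-F arm not asked, *pC* the share of completers who would name a given barrier, and *pN* the share of non-completers.

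- Share in the whole arm = (1 − *s*) × *pC* + *s* × *pN*
- Shortfall from asking completers only = *s* × (*pN* − *pC*), which cannot exceed *s*

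The documents give neither *pC* nor *pN*. The nearest they come to *s* is the recruitment allowance: 120 − 2 × 50 = 20, or 10 per arm, and 10/60 = 16.7%. That is loss from the study over 12 months, not stopping of a 10-week therapy. A person lost at 6 or 12 months may have completed HRV-F and answered, which makes *s* smaller. A person who stops therapy but stays in follow-up is not counted in it, which makes *s* larger.

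Purely to show how the formula behaves, with assumed values:

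| *s* | *pC* 30%, *pN* 60% | *pC* 30%, *pN* 90% |
|---|---|---|
| 5% | 1.5 points | 3 points |
| 16.7% | 5 points | 10 points |
| 30% | 9 points | 18 points |

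These are not forecasts. Statistical methods plans an inductive qualitative analysis for the implementation study, so no prevalence will be estimated. The relevant loss is one of content: a barrier that some completers also mention will surface, whereas one met only by people who withdrew cannot surface through this item.

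**The case against.** The strongest reply is that this is a minor add-on. Secondary objectives defines the implementation study by its stakeholder interviews and survey, and Participants allows up to 100 respondents. Neither source depends on a participant finishing HRV-F. A reader might infer from the completers-only rule that the implementation findings as a whole are biased. The documents do not support that: the selection reaches only the participant-feedback component. This part of the reply stands.

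A reader might also infer that people who stop are not heard at all. That is too strong, given the early barrier monitoring, the weekly calls and the interviews with those who delivered the therapy. What remains true is narrower: apart from the early monitoring, nothing described asks them directly about barriers, and nothing puts these two questions to them.

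Third, completion is not defined. If it means reaching the end of the 10 weeks, participants who attended poorly but did not withdraw would still be asked, and only withdrawals would be missed. This limits the number left out but does not remove the selection.

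Finally, the recruitment allowance might be read as a count of 10 people per arm who stop because of a barrier. It is not: it covers 12 months and includes deaths and other losses. No size can rest on it.

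**Conclusion.** The point holds in a limited form. The rule as written selects the participant feedback towards people who completed HRV-F, and barriers met mainly by those who withdrew may not appear in it. The early monitoring offsets this only for 5 HRV-F participants. The survey, the professional interviews and the randomised comparison are untouched.

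The size is unknown. The documents give no rate of stopping therapy and no barrier frequencies, and the meaning of completion decides how many people are left out. The conclusion rests only on the stated eligibility for the two questions and on the absence, in the article, of any other route that puts them to participants who stop. It is a modest weakness in an ancillary component, worth correcting because the correction is so cheap.

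**What to change.** Change the sentence under Implementation phase so that every participant allocated to HRV-F is asked the two questions: at the end of treatment for those who complete, and at the time of stopping or at 10 weeks for those who do not, by telephone or REDCap link. State what counts as having completed, and report the answers of completers and non-completers separately.

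The questions should go through an unblinded team member. Randomization and blinding keeps assessors blind to allocation, and an answer about the therapy would reveal it.

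The cost is one sentence and two questions, using contact routes already in place. Some who stop will not answer, so the number asked and the number answering should be given for each group. The change is best made before further withdrawals, since reasons for stopping are hard to recover later.

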**Fig. 3 Fig3:**
[figure not shown]
Showing the Implementation at-scale model

#### Socio-demographic, injury and medical assessments

Socio-demographic assessment includes sex, age at the time of initial measurement, level of education and employment history. Injury details include age at the time of the SCI, time (years) since the SCI, level and extent (completeness) of the injury using the International Standards for Neurological Classification of SCI (ISNCSCI; https://asia-spinalinjury.org/isncsci-2019-revision). Medical assessment includes medical history (e.g., pre and post-injury health and psychological status), current medications, body mass index assessed from self-reported height and weight, and classified according to World Health Organization guidelines: < 18.5 kg/m^2^ (underweight), 18.5–24.9 kg/m^2^ (normal), 25–29.9 kg/m^2^ (overweight), ≥30 kg/m^2^ (obese).

### Physiological assessment

See Table 1 for all primary and secondary outcome measures and endpoints (baseline versus 10 weeks, 6 and 12 months) for the RCT and implementation phase. The physiological assessment protocol includes:
(i)Activity #1: 5-min resting baseline (spontaneous breathing) after 2-min habituation;(ii)Activity #2: 5-min Stroop test;(iii)Activity #3: 5-min recovery (spontaneous breathing);(iv)Activity #4: 5-min breathing task (paced breathing at around 6 breath/minute);(v)Activity #5: 5-min recovery (spontaneous breathing).

**Table 1 Tab1:** Schedule of activities and measures for the RCT and implementation study. All psychometric instruments are scientifically validated and reliable

PROJECT STAGE *(number of participants)*			RCT (***N*** = 120) Pilot and main study phase)						Implementation phase (***N*** = 100)
**TIMELINE/PHASES***(D- day, W: week; M: month; Ph: phase)*			**-7D to 0D**	**0D**	**10 W**	**6 M**	**12 M**	**Fortnightly**	**Ph-1 to Ph-5**
**RECRUITMENT**	**ACTIVITIES**	**Mode of data collection**							
Screening	Eligibility checklist	In-person	**✓**						
	ISCoS cardiovascular function dataset	In-person	**✓**						
	ISCoS pulmonary function basic data set	In-person	**✓**						
Consent procedure	Informed consent procedure	In-person	**✓**						
**PARTICIPANT DESCRIPTORS**	**ASSESSMENTS**	**Mode of data collection**							
Socio-demographics	Socio-demographics details	In-person or online		**✓**					
Pre-injury details	Employment history and psychological status	In-person or online		**✓**					
Medical history	Self-report past/present health history	In-person or online		**✓**					
Injury characteristics	Level of lesion, AIS and FIM	Medical records		**✓**					
Pulmonary function	Pulmonary function test	In-person		**✓**					
**ALLOCATION**	**DESCRIPTION**	**Mode**							
Intervention group	HRV-F + Usual care	In-person and online							
Control group	Usual care	Online							
**PRIMARY OUTCOMES**	**OUTCOME MEASURE**	**Mode of data collection**							
Autonomic function	ECG/ HRV Time domain – Short term	In-person		**✓**	**✓**				
	ECG/ HRV Frequency domain – Short term	In-person		**✓**	**✓**				
Cerebral basal artery blood flow	Doppler assessment – Short term	In-person		**✓**	**✓**				
**SECONDARY OUTCOMES**	**OUTCOME MEASURE**	**Mode of data collection**							
Autonomic function	ECG/ HRV Time domain – Long term	In-person		**✓**		**✓**	**✓**		
	ECG/ HRV Frequency domain – Long term	In-person		**✓**		**✓**	**✓**		
	ADFSCI questionnaire	In-person		**✓**	**✓**	**✓**	**✓**		
Cerebral basal artery blood flow	Doppler assessment – Long term	In-person		**✓**		**✓**	**✓**		
Neurophysiological function	Continuous BP	In-person		**✓**	**✓**	**✓**	**✓**		
	EEG	In-person		**✓**	**✓**	**✓**	**✓**		
	NIRS	In-person		**✓**	**✓**	**✓**	**✓**		
	EOG	In-person		**✓**	**✓**	**✓**	**✓**		
	Skin conductance, BVP, respiration and temp	In-person		**✓**	**✓**	**✓**	**✓**		
Secondary health conditions	SCI-SCS	In-person and online		**✓**	**✓**	**✓**	**✓**		
Cognitive function	NUCOG	In-person and online		**✓**	**✓**				
	Stroop test	In-person and online		**✓**	**✓**				
Psychological/mental health function	GADS	In-person and online		**✓**	**✓**	**✓**	**✓**		
	PHQ-9	In-person and online		**✓**	**✓**	**✓**	**✓**		
Psychosocial function	ISCoS pain questionnaire	In-person and online		**✓**	**✓**	**✓**	**✓**		
	FSS	In-person and online		**✓**	**✓**	**✓**	**✓**		
	PSQA	In-person and online		**✓**	**✓**	**✓**	**✓**		
	PCS	In-person and online		**✓**	**✓**	**✓**	**✓**		
Personal factors	*CD-RISC2 Short Form*	In-person and online		**✓**	**✓**	**✓**	**✓**		
Quality of life	*EQ-5D-5L*	In-person and online		**✓**	**✓**	**✓**	**✓**		
Participation and disability	*WHODAS domain – participation items*	In-person and online		**✓**	**✓**	**✓**	**✓**		
Consumer perception and satisfaction	Self-reported perception of change and satisfaction	In-person and online			**✓**				
Costs for Economic evaluation	Self-reported direct and indirect costs	Diaries (up to 12 m)						**✓**	
Adverse events	*Self-monitoring of Adverse events*	Diaries (up to 12 m)						**✓**	
Self-monitoring *of mood, breath rate, pain, fatigue and sleep quality*	*Numeric rating scale (0 to 10)*	Diaries (up to 12 m)						**✓**	
**EXPLORATORY OUTCOMES**	**OUTCOME MEASURE**	**Mode of data collection**							
Personal factors	*WHO ASSIST*	In-person and online		**✓**	**✓**	**✓**	**✓**		
	*COPE inventory – brief*	In-person and online		**✓**	**✓**	**✓**	**✓**		
	*ADAPSS – Short-form*	In-person and online		**✓**	**✓**	**✓**	**✓**		
	*MSES*	In-person and online		**✓**	**✓**	**✓**	**✓**		
Psychological/mental health function	PTSD Checklist 5	In-person and online		**✓**	**✓**	**✓**	**✓**		
Psychosocial function	SSQ6	In-person and online		**✓**	**✓**	**✓**	**✓**		
	Berlin Questionnaire	In-person and online		**✓**	**✓**	**✓**	**✓**		
Environmental factors	*Care, family and compensation status questionnaire*	In-person and online		**✓**	**✓**	**✓**	**✓**		
Participation and disability	*RTW Questionnaire*	In-person and online					**✓**		
**IMPLEMENTATION OUTCOME**	**MEASURE**	**Mode of data collection**							
Qualitative/ quantitative assessment	*Stakeholder interviews and surveys*	In-person and online							**✓**

*Abbreviations*: *ADAPSS* Appraisal of DisAbility Primary and Secondary Scale, *AIS* American Spinal Injury Association Impairment Scale, *ADFSCI* Autonomic Dysfunction Following Spinal Cord Injury, *BP* blood pressure, *COPE* Coping Orientation to Problems Experienced, *CD-RISC2* Connor-Davidson Resilience Scale 2 item short form, *ECG* electroencephaolography, *EEG* Electroencephaolography, *EOG* Electrooculography, *EQ-5D-5L* Euro Quality of Life 5-Dimensional 5-level, *FIM* Functional Impairment Scale, *FSS* Fatigue Severity Scale, *GAD-7* Generalized Anxiety Disorder 7-Item Scale, *HRV* heart rate variability, *ISCoS* International Spinal Cord Society, MH, *MSES* Moorong Self-efficacy Scale, *NUCOG* Neuropsychiatry Unit Cognitive Assessment Tool, *NIRS* Near infrared spectroscopy, *PCS* Pain Catastrophizing Scale, *PHQ-9* Patient Health Questionnaire-9, *PSQA* Pittsburgh Sleep Quality Index, *PCL-5* Post-traumatic Stress Disorder Checklist for the Diagnostic and Statistical Manual of Mental Disorders Fifth Version, *RTW* return to work, *SCI* spinal cord injury, *SCI SCS* Spinal Cord Injury Secondary Condition Scale, *SSQ6* Social Support Questionnaire, *Temp* temperature, *WHO ASSIST* World Health Organisation Alcohol, Smoking, and Substance Involvement Screening Test, *WHODAS* World Health Organisation Disability Assessment Scale

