#### HRV-F training

Ten sessions of formal HRV-F training will be completed over the 10-week intervention. These will involve a mixture of six face-to-face formal sessions (2-h duration each) in the research laboratory and four online/telephone sessions (at-home sessions, up to 1-h duration). Face-to-face HRV-F sessions will be conducted in groups of three participants. However, it is expected that individual sessions will occur given risk of sickness in this population. Self-management strategies will be introduced throughout the 10 weeks of the program, including self-monitoring of mood, anxiety, breath rate, pain/fatigue level and sleep quality, as well as visualisation strategies to be used in conjunction with resonant breathing exercises.

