### Health-related cost, adverse events and monitoring of the mood, breath rate, pain, fatigue and sleep quality

These variables will be measured using a fortnightly participant’s diaries.

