### Statistical methods

Descriptive statistics will be generated for all relevant primary and secondary outcomes at all time-points. Linear mixed models for repeated measures analyses will be used to determine the effectiveness of the HRV-F intervention in autonomic function/HRV and cerebral blood circulation in basal cerebral arteries blood flow. Secondary analyses will determine whether improvements occur in factors such as mental health, cognitive function and sleep associated with the HRV-F intervention. All analyses will be adjusted for factors suspected to confound results, such as education and relevant baseline scores. Latent class mixture modelling will be used to determine trajectories for primary and selected secondary measures like anxiety, depressive mood and quality of life. Missing data will be managed using the linear mixed models, for example, through fitting maximum likelihood estimations generating asymptotically unbiased parameter estimates [68]. Data analyses will be performed using packages such as Statistical Package for the Social Sciences (SPSS version 27, SPSS inc., Chicago, Illinois, USA).

For the implementation study, in which qualitative analyses will also be used, the data will be analysed using valid qualitative packages. Grounded theory, an inductive technique of interpreting the recorded data about the perceptions of the HRV-F and its translation, will be the basis for reaching conclusions about how best to implement and translate the treatment.

For cost-effectiveness, descriptive statistics will be calculated to determine costs and QALYs. The robustness of the costing data will be examined through sensitivity analyses. As in standard economic assessments, costs acquired in this study will likely be skewed, so nonparametric bootstrap methods will potentially be used for testing hypotheses tests and interval estimation. A threshold ICER for Australia will be used to assess value for money.

The ICER will be calculated as per equation (eq. 1) below, that is, the incremental cost per increase in time and frequency domain parameters and as incremental cost per QALY gained in the intervention compared to the controls, in the cost-utility analysis.

1$$ \mathrm{ICER}=\frac{\mathrm{Cost}\ \mathrm{of}\ \mathrm{intervention}\hbox{-} \mathrm{Cost}\ \mathrm{of}\ \mathrm{control}}{\mathrm{Outcome}\ \mathrm{of}\ \mathrm{intervention}\hbox{-} \mathrm{Outcome}\ \mathrm{of}\ \mathrm{control}} $$

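### Table 1 schedules no baseline entry for the 0 to 10 diary ratings (mood, breath rate, pain, fatigue, sleep quality), although endpoints are described as baseline versus later time points

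*Protocol article*

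**What the plan says.** Under Physiological assessment, the protocol article sends the reader to Table 1 for "all primary and secondary outcome measures and endpoints (baseline versus 10 weeks, 6 and 12 months").

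In Table 1, the last three rows under secondary outcomes are collected by diary: costs, adverse events, and self-monitoring of mood, breath rate, pain, fatigue and sleep quality. The self-monitoring row uses a "Numeric rating scale (0 to 10"). The mode for all three rows is "Diaries (up to 12 m"), and each is ticked in the fortnightly column only. The later section on cost, adverse events and monitoring gives the same frequency: "These variables will be measured using a fortnightly participant" diary.

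Statistical methods states: "All analyses will be adjusted for factors suspected to confound results, such as education and relevant baseline scores".

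HRV-F training describes the intervention programme: "Self-management strategies will be introduced throughout the 10 weeks of the program, including self-monitoring of mood, anxiety, breath rate, pain/fatigue level and sleep quality". Home practice lists self-monitoring of the same items among the homework, beside resonant breathing exercises.

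Randomization and blinding places the baseline assessment before randomisation and says that participants are aware of their allocation.

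**The concern.** The ratings are a repeatedly measured symptom outcome, and the table's introduction describes outcomes as baseline against later time points. The schedule provides no day 0 value for them. This goes beyond an article leaving detail to a fuller document, because Table 1 is the collection schedule and it does not fit the endpoint description that introduces it.

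Two things are at stake. Change from baseline on the rating scale itself cannot be calculated, and the analysis loses the covariate likely to be most informative for these ratings.

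There is also a risk of an improvised remedy, in which the first diary entry is treated as the baseline. If that entry comes after randomisation, it is made by a participant who knows the allocation. In the HRV-F arm it may also come after teaching in self-monitoring and resonant breathing has begun. Adjusting for it could remove part of the effect being estimated.

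**Working it through.** **Schedule check (Table 1).**
- Self-monitoring ratings: no tick at 0D, 10 W, 6 M or 12 M; one tick under fortnightly.
- Cost and adverse-event diaries: the same pattern.
- Every other secondary outcome measured more than once (long-term HRV and Doppler, ADFSCI, blood pressure, EEG, NIRS, EOG, skin conductance and respiration, SCI-SCS, NUCOG, Stroop, and the questionnaires): ticked at 0D.
- Perceived change and satisfaction: ticked once, at 10 weeks, and retrospective by nature.

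The five ratings are therefore the only repeated symptom outcome without a scheduled baseline.

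**Number of entries.** Fortnightly over 52 weeks gives 52/2 = 26 entries, of which 10/2 = 5 fall in the 10-week programme. Whether there is also a day 0 entry is not stated.

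**Which diary rows need a baseline.** The economic evaluation compares costs accrued in the study, and the cost-effectiveness ratio is a difference between arms. Adverse events are recorded as they occur during follow-up. Neither needs a baseline value, so the point is confined to the ratings row.

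**Precision.** The documents give no correlation for these ratings, so r is assumed. Let r be the correlation between a pre-randomisation rating and the follow-up quantity compared between arms. Adjusting for that rating alone leaves 1 − r² of the residual variance, which is equivalent to multiplying the sample size by 1/(1 − r²).

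| r (assumed) | Variance removed, r² | Variance left, 1 − r² | Sample-size equivalent |
|---|---|---|---|
| 0.3 | 9% | 91% | 1/0.91 = 1.10 |
| 0.5 | 25% | 75% | 1/0.75 = 1.33 |
| 0.7 | 49% | 51% | 1/0.51 = 1.96 |

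For a given r these figures are upper bounds on the loss. They compare an analysis that has the own-scale baseline with one that has no baseline covariate at all, and the trial does collect related measures at 0D. Repeated diary entries also give a tighter estimate than a single follow-up value would. They do not change the proportion for a given r, but r must then be read as the correlation with the averaged or modelled outcome.

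**Available proxies at 0D.** PHQ-9 for mood; the ISCoS pain items, which are themselves 0 to 10 ratings; FSS for fatigue; the Pittsburgh sleep index; and laboratory respiration for breath rate.

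**The case against.** The strongest reply is that the introductory wording is only a pointer to the table's visit columns. It also covers the implementation phase, which has no such visits, and Table 1 contains another secondary row with no 0D tick. On that reading the diary rows simply have their own schedule. The adjustment sentence names only relevant baseline scores, as examples, and does not promise a same-instrument baseline for each outcome. This has weight and keeps the point minor. It does not supply a baseline for the ratings or say how they are to be compared without one.

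Several stronger readings are tempting, and the documents do not support them:
- A reader might infer that the diaries start only after randomisation. No start is stated; the table gives only the end, at 12 months. What can be said is that no baseline entry is scheduled.
- A reader might extend the point to costs and adverse events. Neither needs a baseline value for a comparison between arms.
- A reader might infer that pre-existing symptoms go unrecorded. Health history, SCI-SCS and ADFSCI are all taken at 0D.
- A reader might conclude that baseline adjustment is impossible or the comparison biased. Randomisation keeps the between-arm comparison unbiased, and a covariate need not come from the same instrument.

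**Conclusion.** The point holds in a narrow form and is minor. As scheduled, the five diary ratings have no baseline on their own scale, so the baseline comparison described for secondary outcomes is unavailable for them on that scale, and some precision is given up. With an assumed correlation of 0.3 to 0.7, the own-scale baseline would remove 9% to 49% of residual variance. The true loss is smaller to the extent that the related 0D measures predict the ratings.

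The conclusion rests on reading the missing 0D tick as meaning that no baseline rating is planned. If the full protocol does take one before randomisation, only Table 1 needs correcting. A first entry made after randomisation is not a safe substitute, because participants know their allocation and the HRV-F programme teaches self-monitoring and resonant breathing.

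The primary outcomes (HRV and Doppler), the power statement and the validated questionnaires on the same constructs are unaffected.

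**What to change.** 1. Take one set of the five 0 to 10 ratings at the baseline assessment, before randomisation, and tick 0D for that row in Table 1.
2. Use that set as the baseline covariate in the mixed model for the ratings.
3. State when the outcome diary starts, and keep the HRV-F homework log separate from it, so that both arms are compared on the same entries.
4. Exempt the cost and adverse-event rows from the baseline-versus-later wording under Physiological assessment.

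For anyone already randomised without a rating, the value cannot be recovered; the matching 0D measure would have to serve as covariate.

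The cost is one short additional rating per participant at a visit already planned, plus an edit to Table 1 and its introductory sentence.
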